### Sample size

Because the present study is a clinical application, according to the actual situation, it is difficult to calculate the sample size by pre-experiment, so we finally decided that the sample size of this study was obtained from the previous relevant literature data. The sample size outcome effect size is based on studies found in the literature using the ODI and NRS scores [21]. The mean change of ODI and NRS in group B is expected to be 93% and 0–1 scores, while in group A it is expected to be 80% and 3–4 scores. The sample size was calculated using the sample size formula for a quantitative equivalence trial: *n* = 2(*Z*_*α*_ + *Z*_*β*_)^2^*δ*^2^/(*D* − Δ)^2^ (*α* = 0.05, *β* = 0.2). After we entered *δ* of 2.17, *D* of 0.1, and *Δ* of 1.2 into the formula, we found that it required 31 patients in each group. Given a loss to follow-up rate of 20%, approximately 76 subjects are required.

This experiment was conducted simultaneously in the Second Spine Department of the Fourth School of Clinical Medicine of Xinjiang Medical University and Spine Department of the First Affiliated Hospital of Shihezi University, and inpatients meeting the inclusion criteria were included in the study.

Since the LSS patient base of the above two departments is large enough to recruit subjects at the same time, there is no need to worry about the sample size. Some benefits can also be provided to patients participating in the study to supplement the sample size (such as free professional counseling, functional exercise instruction)

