### Outcome measures

Multiple outcome measures were utilized which included the NRS (0–10 scale) pain scale and the ODI on a 0–50 scale, with assessment at 1 day, 2 weeks, 3 months, 6 months, and 1 year after the procedure. The Oswestry Disability Index (ODI): back pain-related dysfunction will be assessed using the ODI. The ODI contains 10 questions about daily activities, including inventories of pain intensity, personal care, lifting, walking, sitting, standing, sleeping, sexual life, social life, and traveling. Each question is rated on a scale from 0 to 5 points; the lower the score, the less disabled the person is by the pain. The NRS represented no pain with a 0 and the worst pain imaginable with a 10. NRS is an instrument for the self-assessment of pain and comprises a scale with 0 and 10 at either end of a straight line. The participants marked a point on the line to indicate their level of average pain. The value and validity of the NRS and ODI have been reported [28, 29]. The main outcome measures of the present study were ODI and NRS scores after follow-up and the final recurrence rate calculated according to the requirements. ODI and NRS scores were obtained by designated personnel after follow-up work. After obtaining the above two scoring data, the curative effect was evaluated according to the requirements of Table 4, and the recurrence rate was obtained. According to the ultimate purpose of this study, the recurrence rate plays a very important role in the outcome indicators. ODI and NRS also provide the basis for the final calculation of recurrence rate, which significantly affects the evaluation of the efficacy of each subject, and also plays a decisive role in the research results. Specific criteria for evaluating the efficacy are shown in Table 4.

**Table 4 Tab4:** Efficacy evaluation

Cured: neither CESI nor SNRB cured LSS	
Marked effect: NRS score < 2 points or ODI score < 50%	
Effective: NRS score 2–4 points or ODI score 50–70%	
Relapse: NRS score > 4 points or ODI score > 70% or the use of analgesics of the patient’s own choice	

*Note*: We will record the time a patient has recurrence and stop follow-up

*CESI*, caudal epidural steroid injection; *SNRB*, selective nerve root block; *LSS*, lumbar spinal stenosis; *NRS*, numeric rating scale; *ODI*, Oswestry Disability Index

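### One unconfirmed score above the cut-off is a final relapse and ends follow-up, so ordinary variation overstates recurrence in both arms and removes the data that would show it

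*Protocol article*

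**What the plan says.** Outcome measures, Table 4, sorts patients by their NRS and ODI scores. The two categories that matter here adjoin:

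- "Effective: NRS score 2–4 points or ODI score 50–70" (per cent)
- "Relapse: NRS score > 4 points or ODI score > 70% or the use of analgesics of the patient’s own choice"

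Relapse requires no second reading, no duration and no prior response. The note under the table adds: "We will record the time a patient has recurrence and stop follow-up". Scores are collected "with assessment at 1 day, 2 weeks, 3 months, 6 months, and 1 year after the procedure". Table 4 does not say outright that it is applied at every visit, but an instruction to record the time of recurrence and then stop implies it. On that reading the day-1 score counts too.

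The Hypothesis section and the opening of Methods/design make the recurrence rate the object of the trial, and the Discussion uses it to decide which procedure is more effective. NRS and ODI scores are also main outcomes in their own right.

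Sample size is the only place with expected NRS figures. For the SNRB arm it says "The mean change of ODI and NRS in group B is expected to be 93% and 0–1 scores". The figures for the CESI arm follow in the same sentence: "while in group A it is expected to be 80% and 3–4 scores".

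**The concern.** An NRS of 4 is Effective, and anything above 4 is Relapse. A patient whose pain is stable a little below the line has five chances to be recorded above it, and the first such reading is final. A patient who has not yet responded on day 1 is also a recurrence under the literal rule, without ever having had relief to lose.

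Two things are at stake. First, the reported recurrence rates would mix real loss of effect with reading-to-reading variation, and clinicians would take them as evidence on durability. Second, because follow-up stops, the NRS and ODI series are cut off exactly in these patients. A return to 4 or below at the next visit is never seen, so the error cannot be detected, and the later NRS and ODI means describe only patients who never crossed the line.

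**Working it through.** **Plan's own figure.** The protocol states no expected recurrence rate for either arm, so there is none to reproduce. The check asks how often the rule as written labels a stable patient a relapse.

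**Inputs from the protocol.** Cut-off NRS > 4; five post-procedure visits (both Outcome measures); SD 2.17 and margin 1.2 (Sample size).

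**Assumptions, not in the protocol.** 2.17 is read as the total SD of one NRS reading. The within-patient SD w is 0.5, 1.0 or 1.5. The NRS is continuous, which fits the statement that "The participants marked a point on the line to indicate their level of average pain". Errors are normal and independent between visits, and scores are not truncated at 0 and 10. Only the NRS limb is modelled, since no ODI SD is given.

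**Step 1, one stable patient at level u.** Per-visit probability p(u) = 1 − Φ((4 − u)/w); over five visits 1 − (1 − p)^5.

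| Level u | p at w = 0.5 / 1.0 / 1.5 | At least one of five > 4 |
|---|---|---|
| 3.5 | 0.159 / 0.309 / 0.369 | 58% / 84% / 90% |
| 3.0 | 0.023 / 0.159 / 0.252 | 11% / 58% / 77% |
| 0.5 | 0.000 / 0.000 / 0.010 | 0% / 0.1% / 5% |

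Example: u = 3.0, w = 1.0 gives 1 − (1 − 0.159)^5 = 0.58. If scores are whole numbers, a relapse needs about 4.5 or more, and the row for 3.5 falls to 11% / 58% / 77%. Without the day-1 visit (four visits, continuous) it is 50% / 77% / 84%.

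**Step 2, a whole arm.** Patients' true levels are normal with mean m and between-patient SD b = √(2.17² − w²) = 2.11 / 1.93 / 1.57. A false relapse is a true level of 4 or below with at least one reading above 4, that is, 1 − (1 − p(u))^5 integrated over u ≤ 4. With a second independent reading required, the integrand is 1 − (1 − p(u)²)^5. Percentages are of all patients in the arm.

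| | w = 0.5 | w = 1.0 | w = 1.5 |
|---|---|---|---|
| Mean 3.5: true level > 4 | 40.6 | 39.8 | 37.5 |
| Mean 3.5: any reading > 4 | 51.5 | 62.7 | 74.7 |
| Mean 3.5: false relapse | 10.9 | 23.1 | 37.4 |
| Mean 3.5: false relapse, confirmed rule | 4.2 | 9.1 | 16.1 |
| Mean 0.5: true level > 4 | 4.9 | 3.5 | 1.3 |
| Mean 0.5: any reading > 4 | 8.6 | 12.6 | 17.2 |
| Mean 0.5: false relapse | 3.8 | 9.2 | 16.0 |
| Mean 0.5: false relapse, confirmed rule | 1.3 | 2.7 | 3.7 |

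Confirmation also misses some patients whose true level is above 4: at mean 3.5 about 0.6 / 1.3 / 2.2 points.

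**Step 3, the contrast between arms** (single-reading rule against true level > 4, in the order w = 0.5 / 1.0 / 1.5).

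| Mean levels | True difference | Difference under the rule | Risk ratio, true → rule |
|---|---|---|---|
| 3.5 v 0.5 | 35.8 / 36.3 / 36.2 | 42.9 / 50.1 / 57.5 | 8.3 / 11.5 / 29.3 → 6.0 / 5.0 / 4.3 |
| 3.5 v 2.3 (gap 1.2) | 19.6 / 20.9 / 23.6 | 21.5 / 23.1 / 24.1 | 1.9 / 2.1 / 2.7 → 1.7 / 1.6 / 1.5 |
| 3.5 v 3.5 | 0 | 0 | 1 → 1 |

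The absolute difference grows by about 7 to 21 points in the first row, by about 0.5 to 2 in the second and not at all in the third.

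**The case against.** The rule is the same for both arms, participants are blinded, and evaluation of results is stated to be blinded, so the rule cannot create a difference where there is none. This stands, and Step 3 shows it.

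A reader might nevertheless infer that the rule works in favour of the hypothesis: CESI patients are expected at NRS 3–4, just under the line, and SNRB patients at 0–1, so false relapses would arise almost only in group A. The documents do not support that as a general statement, for three reasons.

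- Sample size calls these figures a mean change. If everything in that sentence is a change, group A improves more than group B on the NRS, against the hypothesis and against the 93% and 80% beside it. If everything is a level, ODI 80% and 93% put both arms above the 70% relapse line. Only a mixed reading (ODI as change, NRS as level) places group A at 3–4. It is plausible, but it is an interpretation.
- The same section enters a true difference of 0.1 into an equivalence formula, which does not fit a gap of about three points.
- False-relapse figures of 18% / 58% / 76% in group A and 0% / 0% / 2% in group B can be produced (whole-number scores, w = 0.5 / 1.0 / 1.5), but only by placing every patient within 3–4 or 0–1. With the spread implied by 2.17, the low-level arm has false relapses too.

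It is also fair that patients report average pain, which damps short fluctuations, and that positive correlation between visit errors would lower the figures. Both affect the size. Neither supplies the missing confirmation or restores the lost follow-up.

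**Conclusion.** The concern holds as a defect in the event definition. Relapse rests on one unconfirmed score with no buffer above Effective, and it is made irreversible by stopping follow-up. Recurrence is therefore overstated in both arms: by roughly 11 / 23 / 37% of patients at a mean level of 3.5 and 4 / 9 / 16% at 0.5, for an assumed within-patient SD of 0.5 / 1.0 / 1.5.

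These sizes rest on the listed assumptions, above all a within-patient SD that the protocol does not give. The untruncated normal model is crudest for the low-level arm.

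A one-sided gain for SNRB is not established. On the absolute scale it appears only if the Sample size figures are post-treatment levels. It nearly vanishes at a gap of 1.2 and is absent at equal levels, and wherever the arms differ the risk ratio moves towards 1.

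**What to change.** 1. Replace the stopping note under Table 4: a first score above the cut-off does not end follow-up, and NRS and ODI are collected at all scheduled visits whatever the relapse status.
2. Count a score-based relapse (NRS > 4 or ODI > 70%) only when a second score, taken shortly afterwards by the same assessor on the same instrument, is also above the cut-off. Date the relapse to the first reading. The analgesic criterion is not touched by this change.
3. State in Table 4 at which visits the rule applies, and whether day 1 is one of them.
4. Report the single-reading definition as a sensitivity analysis.
5. State in Sample size whether 3–4 and 0–1 are levels or changes.

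**Cost.** One short extra score per suspected relapse. At mean levels 3.5 and 0.5, the share of patients with at least one reading above 4, averaged over two equal arms, is (51.5 + 8.6)/2 = 30%, (62.7 + 12.6)/2 = 38% or (74.7 + 17.2)/2 = 46%, so about 23, 29 or 35 of 76 patients would need at least one. The rule that data are collected within 24 hours of the specified date needs an allowance for this score. Brief relapses that resolve before the second score no longer count. The visits in item 1 are already scheduled. Trial status gives April 2020 as the start of recruitment, so where follow-up has already been stopped the missing scores cannot be recovered, and the report should say how many patients this concerns.

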## Methods/design

This is a randomized controlled trial, aimed at comparing the recurrence rate of LSS following treatment with SNRBs and CESIs in patients with one-level LSS. This study was approved by the Ethics Committee of the Fourth School of Clinical Medicine of Xinjiang Medical University and will be conducted in accordance with the World Medical Association Declaration of Helsinki. This study is registered in the Chinese Clinical Trial Registry (Registration No. ChiCTR1900028038). Written informed consent will be obtained from all patients before initiating treatment.

Evaluation of the results and statistical analysis will be performed by professionals who are blinded to the group assignment. Participant flow is shown in Fig. 1. The study will last for 1 year. Patients will be randomly divided into two groups with patients in group A receiving a CESI and patients in group B receiving an SNRB.

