### Randomization and blinding

[name] and [name] from the Spine Department of the First Affiliated Hospital, School of Medicine, Shihezi University, will use computer software to generate random sequences, which will be sealed in envelopes and concealed from recruiters and subjects. [name] from the Second Spine Department and investigator [name] are responsible for recruiting eligible patients. [name] from the Second Spine Department will randomly assign recruited patients into two groups. In this study, we will use the single-blind approach in which the participant is unaware of which treatment he/she is receiving. The specific procedure performed will be kept hidden from all participants before unblinding.

We also plan to charge all subjects the same fee to ensure the nature of blinding. The specific fees charged are as follows: nerve blocks 86 yuan + 2 vials of triamcinolone acetonide injection (40 mg/ml, Kunming Jida Pharmaceutical Co., Ltd.), 18.98 yuan + 1 vial of lidocaine (20 mg/ml, Hebei Tiancheng Pharmaceutical Co., Ltd.), and 2.62 yuan + 1 vial of Omnipaque (300 mg I/ml, GE Healthcare, Shanghai, China) (83 yuan). The total cost is 190.6 yuan.

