For the control group and the experimental group, other treatments allowed for the patients are as follows: (1) both groups can be given routine nursing treatment in Department II of Spine of Traditional Chinese Medicine Hospital of Xinjiang Uygur Autonomous Region, including daily inquiry of patients’ condition, pain improvement, and care for patients. (2) Acupuncture and moxibustion treatment of lumbar spinal stenosis was performed by a doctor designated by the Acupuncture and Moxibustion Department of the said hospital. Standardized acupuncture and moxibustion treatment of lumbar spinal stenosis was adopted, that is, acupuncture and moxibustion treatment was the same for all subjects. (3) The massage treatment of lumbar spinal stenosis was performed by the designated physician in the Department of Massage of the said hospital. The standardized treatment of lumbar spinal stenosis with acupuncture and massage was used, that is, all subjects had the same massage treatment. (4) The treatment can be performed by the designated nurse of Department II of Spine and ensure that all subjects are electrically treated in the same position. The other treatments allowed are traditional Chinese medicine treatment, which can play the role of adjuvant treatment, and the two groups of patients received the same treatment. As a result, the effect of the above treatment on the experimental results can be avoided. For the control group and experimental group, the other treatments prohibited from the patients are as follows: (1) In the course of the experiment, other invasive treatments for lumbar spinal stenosis were performed, (2) It is forbidden for the subjects to take drugs that can improve the clinical symptoms of lumbar spinal stenosis. (3) Patients were not allowed to receive other treatments for lumbar spinal stenosis without the consent of the researcher. (4) They took related analgesics by themselves.

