### Dropouts and loss to follow-up

All patients have the right to drop out of the study at any time. If a patient chooses to discontinue participation, we will withdraw consent from this patient and terminate the study. The chief investigator can also terminate a subject’s participation if he/she breaks the rules governing this study or has severe adverse events. Data on these subjects will be excluded from our final analysis.

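### The exclusion rule lets a patient who has relapsed by taking analgesics be removed from the recurrence analysis as a rule-breaker

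*Protocol article*

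**What the plan says.** Four parts of the protocol article bear on the point.

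- **Outcome measures, Table 4.** The relapse category reads "Relapse: NRS score > 4 points or ODI score > 70% or the use of analgesics of the patient’s own choice". The three criteria are joined by *or*, so analgesic use suffices without any NRS or ODI threshold being crossed. The note to the table adds "We will record the time a patient has recurrence and stop follow-up".
- **Supervision, safety, and quality control.** The treatments prohibited in both groups include, as item 2, "It is forbidden for the subjects to take drugs that can improve the clinical symptoms of lumbar spinal stenosis" and, as item 4, "They took related analgesics by themselves".
- **Dropouts and loss to follow-up.** "The chief investigator can also terminate a subject’s participation if he/she breaks the rules governing this study or has severe adverse events". The sentence that follows is "Data on these subjects will be excluded from our final analysis".
- **Blinding.** Under Methods/design: "Evaluation of the results and statistical analysis will be performed by professionals who are blinded to the group assignment". Under Randomization and blinding: "we will use the single-blind approach in which the participant is unaware of which treatment he/she is receiving". Neither statement names the chief investigator.

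The Hypothesis section makes recurrence the outcome on which SNRB is expected to do better than CESI.

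**The concern.** One act, taking an analgesic on one's own initiative, is both an endpoint event and a breach that can lead to exclusion from the analysis. Nothing in the protocol says which rule takes precedence. A patient handled under the dropout section leaves both the numerator and the denominator of the recurrence rate. This is exclusion on the outcome itself, decided after the event and at one person's discretion.

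The rate falls in any arm where the rule is used. The comparison between arms is distorted on the odds-ratio scale if the rule removes a different share of relapses in each arm. No part of the protocol shows that the shares would differ, and none prevents it. With about 31 analysed patients per arm, a handful of such decisions is enough to move the estimate of the hypothesis outcome.

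**Working it through.** **1. The texts side by side**

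| Question about a patient who takes own-choice analgesics | Answer in the protocol | Section |
|---|---|---|
| Has the patient relapsed? | Yes, on this criterion alone | Outcome measures, Table 4 |
| What happens next? | Recurrence time is recorded and follow-up stops | Note to Table 4 |
| Was the act allowed? | No (items 2 and 4) | Supervision, safety, and quality control |
| Can a rule-breaker be terminated? | Yes, at the chief investigator's discretion | Dropouts and loss to follow-up |
| Are a terminated subject's data analysed? | No, without exception | Dropouts and loss to follow-up |

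The note to Table 4 governs follow-up. The only sentence among these that governs who enters the analysis is the exclusion sentence, and it is unqualified.

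**2. Inputs for an illustration**

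- The analysed number per arm, *n* = 31, is taken from the Sample size section. It does not follow from the formula printed there. With two-sided α = 0.05 and β = 0.2, 2(1.960 + 0.842)² × 2.17² / (0.1 − 1.2)² = 61.1, that is 62 per group; one-sided α gives 48.1, that is 49. That is a separate matter. Here 31 serves only as the planned size of the analysis, and the argument in step 1 does not depend on it.
- The protocol gives no relapse rates and no rates of analgesic use. All relapse counts *r* and exclusion counts *x* below are assumptions.

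**3. Formulas**

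After *x* of *r* relapses are excluded in an arm:

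- observed rate = (*r* − *x*) / (31 − *x*)
- observed odds = (*r* − *x*) / (31 − *r*), since the non-relapsed patients are untouched
- observed odds ratio (SNRB/CESI) = true odds ratio × (share of relapses kept in SNRB) / (share kept in CESI)

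The odds ratio is therefore unchanged exactly when (*r* − *x*)/*r* is the same in both arms.

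**4. Results with an assumed true difference (15 CESI and 9 SNRB relapses)**

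| Excluded CESI / SNRB | CESI | SNRB | Difference (points) | Odds ratio |
|---|---|---|---|---|
| 0 / 0 | 15/31 = 48.4% | 9/31 = 29.0% | 19.4 | 0.436 |
| 5 / 3 (one third of each) | 10/26 = 38.5% | 6/28 = 21.4% | 17.0 | 0.436 |
| 3 / 1 | 12/28 = 42.9% | 8/30 = 26.7% | 16.2 | 0.485 |
| 2 / 2 | 13/29 = 44.8% | 7/29 = 24.1% | 20.7 | 0.392 |
| 1 / 3 | 14/30 = 46.7% | 6/28 = 21.4% | 25.2 | 0.312 |

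Check of the 3 / 1 row: 0.436 × (8/9)/(12/15) = 0.436 × 1.111 = 0.485.

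The 2 / 2 row shows that equal counts are not equal shares: two of nine is a larger share than two of fifteen, so the odds ratio moves away from 1. In the 5 / 3 row the shares are equal and only the rates and their difference shrink. That shrinkage of the difference holds at the rates assumed here; it need not hold at very high relapse rates.

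**5. Results with no true difference (12 relapses in each arm, 38.7%)**

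| Excluded CESI / SNRB | CESI | SNRB | Odds ratio |
|---|---|---|---|
| 2 / 2 | 10/29 = 34.5% | 10/29 = 34.5% | 1.00 |
| 3 / 1 | 9/28 = 32.1% | 11/30 = 36.7% | 1.22 |
| 1 / 3 | 11/30 = 36.7% | 9/28 = 32.1% | 0.82 |

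**The case against.** The strongest reply is that the more specific rule already settles the case. Table 4 names this very event as relapse, its note says to record the time and stop, and the Discussion repeats that time to relapse will be recorded and the recurrence rate calculated from it. Once follow-up has ended as a recurrence, little participation is left to terminate. That is a sensible reading and may well be the intended one. It does not remove the problem: the note is about follow-up, the breach and the relapse occur at the same moment, and the exclusion sentence carries no exception.

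Second, the dropout section does not mention analgesics or define which rules it means, so the link through the prohibited-treatment list is an inference. That is true. But a list of treatments forbidden to trial patients is a natural member of the rules governing the study. Forbidding rescue medication and also counting its use as failure is not a contradiction; the trouble comes only when the exclusion sentence is added.

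Third, no bias between arms is shown. The prohibitions apply to both groups, participants are blinded, and the unequal splits above are chosen for illustration and point in both directions. This stands. The silence about the chief investigator's blinding shows only that the text offers no safeguard there, not that this person knows the allocation.

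Fourth, analysis sets are often left to an analysis plan. Here, though, the protocol already fixes the exclusion in an explicit sentence, and a plan that kept these patients would contradict it.

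**Conclusion.** The concern holds as a defect in a stated rule. As written, the protocol permits a patient who has met the recurrence endpoint by taking self-chosen analgesics to be terminated and dropped from the analysis of the outcome named in the hypothesis. It does not show that this is intended or would be routine.

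The size cannot be determined from the document. Under the assumed counts with 31 per arm, four excluded relapses move an odds ratio of 0.44 to between 0.31 and 0.48, and a true odds ratio of 1.00 to 0.82 or 1.22, according to the split between arms. Equal shares excluded leave the odds ratio unchanged but still lower both recurrence rates. The direction of any bias is unknown. The point should be fixed, because the remedy is cheap and the affected outcome is central; confidence is medium, because the alternative reading of Table 4 is reasonable.

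**What to change.** Amend the section Dropouts and loss to follow-up, before the data are analysed, along these lines:

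> No randomised patient is excluded from the analysis because of a breach of the study rules. Use of analgesics as defined in Table 4 counts as relapse on its recorded date, and the patient is analysed in the assigned arm.

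Leave the relapse definition in Table 4 as it is, without a new restriction by indication, and keep the list of prohibited treatments as a rule of conduct. The change does not touch exclusions after voluntary withdrawal or severe adverse events, which the same sentence also covers and which deserve their own look.

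The cost is one or two sentences and slightly more analysis work. No new data item is needed: the Table 4 definition already requires that analgesic use be known, and its note and the Discussion already require the recurrence time to be recorded.

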### Hypothesis

Our hypothesis is that SNRBs have a lower recurrence rate than CESIs in treating patients with single-level LSS.

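### Taking self-chosen analgesics is both a relapse and a rule violation that can lead to exclusion, and the protocol does not say which rule prevails

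*Protocol article*

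**What the plan says.** Three rules in the protocol article apply to a patient who takes painkillers on his or her own initiative.

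- **Outcome measures, Table 4:** "Relapse: NRS score > 4 points or ODI score > 70% or the use of analgesics of the patient’s own choice". The criteria are joined by *or*, so analgesic use is sufficient by itself. The note to the table adds: "We will record the time a patient has recurrence and stop follow-up".
- **Supervision, safety, and quality control, list of prohibited treatments:** item (4) reads "They took related analgesics by themselves". The phrasing is awkward, but its place in the list makes the meaning clear. Item (2) is wider: "It is forbidden for the subjects to take drugs that can improve the clinical symptoms of lumbar spinal stenosis".
- **Dropouts and loss to follow-up:** "The chief investigator can also terminate a subject’s participation if he/she breaks the rules governing this study". The section ends: "Data on these subjects will be excluded from our final analysis".

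Recurrence is the outcome on which the trial's hypothesis rests: "Our hypothesis is that SNRBs have a lower recurrence rate than CESIs". The Outcome measures section also names it as a main outcome.

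**The concern.** Under Table 4, a patient who takes analgesics has had the endpoint event. Under the prohibited list, that patient has also broken a study rule, and the dropout section then allows removal from the analysis. Removing such a patient selects the analysis set on the outcome itself, after randomization. The retained patients in each arm would then be partly those who did not relapse by this route, and the comparison would no longer be between the groups as randomized.

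The choice is left to case-by-case discretion with no criterion. Two patients with identical histories could be handled differently, one as a relapse and one as a deletion. The trial is small (about 76 subjects in total), so each such decision has a visible effect on an arm's recurrence rate.

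**Working it through.** **Step 1: follow one patient through the rules.** Take a patient who, between two visits, takes an analgesic of his or her own choosing and has no other Table 4 criterion.

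| Rule | Consequence |
|---|---|
| Table 4 and its note | Relapse; time recorded; follow-up stops |
| Prohibited treatments, item (4) | Breach of a study rule |
| Dropouts and loss to follow-up | Chief investigator may terminate; if so, data are excluded |

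If the first rule is applied alone, the patient is in the numerator and the denominator of the recurrence rate. If the third is applied, the patient is in neither. No sentence exempts a relapse from the exclusion, and none gives Table 4 priority. The exclusion covers the subject's data, not only data after termination, so a relapse already recorded is not protected because follow-up has ended.

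**Step 2: the effect of one deletion on an arm's rate.** The plan has no recurrence figure to reproduce. The inputs are the planned total of 76 (Sample size section), an inferred 38 per arm (76/2; equal groups are implied because the section gives one required number for each group), and assumed numbers of relapses.

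With x relapses among n patients, deleting one relapse instead of counting it lowers the rate by

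x/n − (x − 1)/(n − 1) = (n − x)/(n(n − 1)).

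For n = 38 the denominator is 38 × 37 = 1406:

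| Relapses x (assumed) | Counted | Deleted | Drop |
|---|---|---|---|
| 1 | 1/38 = 2.6% | 0/37 = 0% | 37/1406 = 2.6 points |
| 8 | 8/38 = 21.1% | 7/37 = 18.9% | 30/1406 = 2.1 points |
| 15 | 15/38 = 39.5% | 14/37 = 37.8% | 23/1406 = 1.6 points |

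With the 31 per group that the Sample size section requires before allowing for losses, n(n − 1) = 930, and the drop is 30/930 = 3.2 points for a single relapse and 19/930 = 2.0 points for one of 12.

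**Step 3: direction.** As long as some patients in an arm have not relapsed, the drop is positive, so a deletion always lowers the rate of the arm in which it occurs. A deletion in the caudal arm reduces the caudal-minus-nerve-root difference, and a deletion in the nerve root arm increases it. The net effect depends on how many analgesic relapses are deleted in each arm, and the documents give nothing from which to estimate that.

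**The case against.** The best defence is that the rules are compatible. A forbidden rescue drug can sensibly also be a failure event: it is not allowed, and if taken it counts as relapse. Table 4 is the specific rule for self-chosen analgesics. The termination clause is general, is worded as a permission, and sits in a section on dropouts. On a natural reading the specific rule governs, and follow-up has already stopped. This reading is reasonable and may be what the investigators intend, but it is not written, and the exclusion sentence carries no exception. Nor is this a detail left to an analysis plan, because the article itself fixes both the endpoint rule and the exclusion rule.

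Other parts of the defence stand and limit the point:

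- A reader might infer that every analgesic user will be excluded. The text does not say so; exclusion follows only if the chief investigator chooses termination.
- A reader might extend the contradiction to invasive treatment (prohibited item (1), "other invasive treatments for lumbar spinal stenosis were performed") and to other symptom-relieving drugs. These are not Table 4 events, so excluding such patients does not by itself delete a protocol-defined relapse. Adding them to the endpoint would be a redesign open to debate.
- A reader might infer decisions made with knowledge of the arm. The article states that participants, outcome evaluators and analysts are blinded. It is silent on the chief investigator, and silence in a condensed article does not show that this person is unblinded.

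**Conclusion.** The conflict is real and lies in the stated rules. One act is both sufficient for the hypothesis endpoint and a ground for removal from the analysis, with no order of precedence. It should be resolved before the data are analysed.

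Its size is unknown. The figure of about 1.6 to 2.6 points per deleted relapse is a sensitivity calculation that rests on 38 per arm and on between 1 and 15 relapses in that arm; it is not an estimate of expected bias. A reader might infer that the ambiguity favours nerve root blocks, or that it would reverse the trial's conclusion. The documents support neither, since they give no recurrence rate, no rate of self-medication, and no indication of how terminations would fall between the arms.

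**What to change.** Add to the section on dropouts and loss to follow-up:

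*A subject who meets any Table 4 relapse criterion, including use of self-chosen analgesics, is counted as a relapse in the randomized group, dated at that event, and is not excluded from the analysis for that rule violation. For other rule-breakers whose participation is terminated, data collected up to termination are kept in the analysis.*

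The Table 4 definition stays as it is. Because Table 4 asks for no reason for analgesic use, the new text should not ask for one either. A reason test would bring discretion back and leave some Table 4 relapses open to exclusion.

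The cost is small. Sample size, visits and interventions do not change, and the time of recurrence is already to be recorded. Reported recurrence rates may be slightly higher than if such patients were removed. Recruitment began in April 2020 and completion was expected by the end of 2021, so the rule should also be applied to any subject already terminated for analgesic use, and the amendment should be dated before the analysis.
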